## Abstract

**Background:**

A considerable number of terminally-ill adult children are outlived by at least one parent and receive palliative care prior to their death. At the same time, adult children continue to be confronted with their parents’ terminal illnesses and end-of-life situations. The current study explores the specifics of dyadic interaction at the end of life between a) adult children suffering from a life-threatening disease and their parents, and b) terminally ill parents and their adult children.

**Methods:**

This prospective observational study aims at filling the existing gap on adult child-parent interaction specifics at the end of life using an exploratory mixed-methods framework. The mixed-methods framework combines a qualitative face-to face interview and quantitative self-report questionnaires to study the topic at hand. The qualitative interview will focus on experiences, expectations, and wishes with regard to dyadic communication, information about illness and prognosis, expressed and perceived burden and support as well as caregiving role at the end of life. The questionnaires will cover socio-demographics, loneliness, attachment style, social support, and emotional closeness.

**Discussion:**

The research group is currently adjusting a semi-structured interview guide and questionnaire instructions based on the results of a multiprofessional scientific advisory board meeting (Jan. 2018). In a next step, and prior to qualitative and quantitative data collection, the questionnaires will be piloted on patients and their family members in a palliative care setting. The main expected results are i) a description of the specifics of the interaction within and between both dyads, ii) the development of hypotheses and a theoretical framework on the specifics, similarities, and differences for both study groups, and iii) clinical conclusions on specific psychosocial care needs of both groups.

**Trial registration:**

The study was registered prospectively in the Health Services Research Germany register (Versorgungsforschung Deutschland – Datenbank) (Registration N° VfD_Dy@EoL_17_003897; date of registration: November 22, 2017) and in the German Clinical Trials Register (Deutsches Register Klinischer Studien) (Registration N° DRKS00013206; date of registration: October 27, 2017). The study is visible in the International Clinical Trials Registry Platform Search Portal of the World Health Organization under the German Clinical Trials Register number.

## Background

With an aging society, the number of parents who are confronted with the death of their adult child is rising. In Germany, approximately 16,000 adults die every year before the age of 45 [1]. A considerable percentage of them is being survived by at least one parent and receives palliative care (PC) prior to their death. At the same time, adult children continue to be confronted with their parents’ terminal illnesses and end-of-life (E-o-L) situations. According to the World Health Organization definition, PC seeks to improve the quality of life of both patients and their families facing life-threatening illness [2]. In line with this principle, the current study will apply a dyadic framework to examine interaction specifics at the end of life (EoL) between a) adult children suffering from a life-threatening disease and their parents and b) terminally ill parents and their adult children.

### Investigating interaction in dyads of parents and adult children

The current study focuses on the subpopulation parents-adult children since this dyad may face specific challenges with regard to communication, information about illness, expressed and perceived burden and support as well as caregiving role during PC hospitalization. So far, there is a paucity of data on interactions between parents and adult children at the EoL even though personalized health care is becoming increasingly popular. Likewise, no evidence-based psychosocial interventions exist for this dyad. Retrospective case studies examining psychosocial and physical health outcomes and levels of disordered grief found parents to experience mental and physical health impairment following their child’s life-threatening diagnosis and subsequent death [3]. Examining the specifics of the interaction between adult children suffering from a life-threatening disease and their parents in comparison to the interaction of terminally ill parents and their children may provide better understanding of the distinct psychosocial needs of both dyads and may decrease the likelihood of developing negative health outcomes while increasing quality of life.

Being the relative of a terminally ill family member (FM) can become emotionally, physically, and socially stressful [4–10]. Amongst other aspects, caregivers of PC patients are challenged by fear of loss, mental health problems, and trouble sleeping [5, 6, 8, 10]. Studies assessing patients’ quality of life and burden on family caregivers generally reported interdependencies between the two. One study [11] found a relationship between burden perceived by family caregivers and patients’ feelings of anxiety and depression. Another study [10] showed increases in caregivers’ depression and perceived burden as a function of patients’ declining functional status. Additional challenges in interaction at the EoL may be faced by adult children who have been diagnosed with a life-limiting disease and by their surviving parents. Parents of terminally ill adult children experience not only a multiplicity of intense emotional feelings including uncertainty, helplessness, and injustice over the reversed natural order of death [12–16], but they also report being excluded from their child’s decision-making process [16]. This may result in uncertainty and loss of control with regard to the course of the disease, treatment effects, and time left with their sick child. Another burdensome factor is the lack of open communication about illness and fears between sick children and parents [14, 16]. The child’s life-limiting disease may further trigger the parental wish to provide care for their adult child and to be present at the time of death. This desire may be in conflict with their adult child’s sense of autonomy and the desire of their child’s romantic partner to serve as a main caretaker [12, 17]. Hence, parents describe a transformation of the parent role from an active and directive caregiving role to a more passive one [3]. Likewise, interactions between terminally ill parents and their children can be challenging. Research findings suggest parents’ struggle to tell their children about the serious medical condition in order to avoid distress and burden in their loved ones. Not telling, in turn, can cause emotional disturbances in their children [18]. So far, most investigators have examined burden and challenges in FMs and patients separately, but no study has focused on the interaction between patient and FMs, and, in particular, the relationship between parents and adult children. Examining the specifics of interaction between adult children suffering from a life-threatening disease at the EoL and their parents in comparison to the interaction of terminally ill parents and their children may provide a better understanding of the distinct psychosocial needs of both dyads.

## Study aims

The current research project seeks to explore the specifics of the interaction between a) adult children suffering from a life-threatening disease and their parents at the EoL in comparison to the interaction of b) terminally ill parents and their adult children. Both within-dyad as well as between-dyad interaction will be investigated. Detailed hypotheses regarding within-dyad differences are as follows: 1) Differences in the specifics of interaction in terms of communication, information about illness, expressed and perceived burden and support as well as caregiving role can be found between terminally ill children and their healthy parents. 2) Differences in the specifics of interaction can also be found between terminally ill parents and their healthy children. Pertaining to between-dyad differences, the authors want to explore the following hypothesis: 3) Differences with regard to the specifics of the interaction can be found between the two dyads (terminally ill children – healthy parents vs. terminally ill parents – healthy children).

Innovative aspects of this research project are, first, the topic under investigation which has not been systematically investigated to date. To the authors’ knowledge, no study exists which has explored the specifics of interaction in and between dyads of a) terminally ill children and their healthy parents, and b) terminally ill parents and their healthy children. Second, no evidence-based psychosocial intervention programs have been developed for both terminally ill adult children and their parents, as well as for terminally ill parents and their adult children. Third, the parallel use of quantitative and qualitative methods allows broadening the spectrum of information through the use of a multi-level and multi-perspective approach.

## Aims of study protocol

Research on interaction patterns of parents and their terminally ill adult children and adult children and their terminally ill parents raises a number of complex issues. These include field access, the challenge of recruiting parent-child dyads instead of independent individuals for study participation, the use of mixed methods, and the measurement of outcomes. The study protocol at hand is designed to shed light on these issues. Furthermore, the study protocol addresses ethical considerations, the subject of data security, and dissemination of study results.

## Methods and design

This study is a prospective observational study and aims at filling the gap on adult child-parent interaction specifics using an exploratory mixed-methods framework. The mixed-methods framework combines a qualitative semi-structured in-depth face-to-face interview and quantitative self-report questionnaires. Qualitative and quantitative data will be collected simultaneously in both dyads. Gysels et al. [19] have shown that qualitative interviews are suitable for PC patients and caregivers as they had therapeutic and empowering effects on participants.

The qualitative interview will focus on experiences, expectations, and wishes with regard to dyadic communication, information about illness and prognosis, expressed and perceived burden and support as well as caregiving role at the EoL. The questionnaires will cover socio-demographics, loneliness, attachment style, social support, and emotional closeness. Participants will provide information about their age, gender, citizenship, education, employment, relationship status, living arrangements, children, and primary caretaker responsibilities. Participants’ feelings of loneliness and social isolation are measured by the revised University of California, Los Angeles (UCLA) Loneliness Scale [20, 21]. The scale consists of 20 items for which participants rate how often they feel lonely or socially isolated on a Likert-type scale from 1 (never) to 4 (often). The Experiences in Close Relationships Scale (ECR) [22, 23] is a 36-item self-report measure that assesses individual differences with respect to attachment-related anxiety and attachment-related avoidance. Items are rated on a 7-point Likert scale from 1 (strongly disagree) to 7 (strongly agree). The 52-item Berlin Social Support Scales (BSSS) [24] measure six dimensions of cognitive and behavioral aspects of social support on a four-point Likert scale ranging from 1 (strongly disagree) to 4 (strongly agree). The Graphic closeness scale (GCS) [25] assesses individuals’ closeness on a one-dimensional line with oneself as anchor point. The scale ranges from 100 (very close) to 0 (not close = very distant).

A multiprofessional scientific advisory board (i.e. 9 experts from the fields of medicine, psychology, sociology, psychotherapy, medical ethics, hospice and PC work as well as bereavement, grief, and PC research) met in person on January 15, 2018 to provide valuable input for the research group on the development of the semi-structured interview guide, the selection of validated psychological questionnaires, and the refinement of recruitment strategy and cooperation practices. Furthermore, the board members made suggestions with regard to the socio-demographic questionnaire as well as questionnaire instructions in terms of clarity and methodological barriers.

### Study population and data collection

Study participants will be recruited via a German university medical center and further hospice and palliative care service providers. So far, three partners have agreed to aid in recruitment process. Further recruitment partners will be integrated during the course of the study if indicated. The ethics approval covers the integration of additional recruitment partners. Potential study eligibility will be assessed by the project managing study coordinator following the admission of a patient to the medical center’s PC unit, which holds seven beds, or to other cooperating wards or services offering E-o-L- care. Potential participants who meet the inclusion criteria (see section “Inclusion, exclusion, and termination criteria”) will be approached by a researcher. The researcher will invite both patient and FM/s to participate in a face-to-face interview and to fill in a set of questionnaires at the PC unit.

Due to the partly qualitative nature of this study, no precise sample size estimates or power calculations can be made at this point. Data collection will end once data saturation is obtained. Data saturation is achieved for the interviews when no more new or valuable information can be attained, further coding is no longer feasible, and once the study can be replicated [26, 27]. Existing exploratory qualitative studies in the area of grief and bereavement and palliative [12, 28–30] as well as qualitative research methods guidelines suggest that approximately 12 interviews are necessary to identify 90% of analysis codes [26]. The general patients’ and families’ willingness to participate in research is surprisingly high in palliative and E-o-L care [31]. Hence, inclusion of 12 to 20 terminally ill children and their parent/s as well as 12 to 20 terminally ill parents and their child/ren (a total of 24 to 40 patients and 24 to 40 FMs) for the qualitative interview and questionnaire battery is feasible. Hospice and PC cooperation partners will support study recruitment. So far, one hospital and one nursing service agreed for study cooperation. All study participants will be interviewed separately. If terminally ill children are survived by both parents and if terminally ill parents are survived by more than one adult child, all eligible FMs will be invited to participate in the face-to-face interview and to complete questionnaires during PC hospitalization or when receiving palliative or hospice care.

The collection of quantitative questionnaire data will be continued in both dyads even if saturation of qualitative interview data is reached. The assessment of a higher number of both described dyads enables better specification of the number of affected patients and FMs as well as testing of hypotheses and interrelations developed from qualitative data.

### Inclusion, exclusion, and termination criteria

Inclusion criteria for dyad *terminally ill children and healthy parents* comprise terminally ill patients 18 years of age or older who are seeking palliative or hospice care and who are in contact with at least one living parent, and for dyad *terminally ill parents and healthy children*, inclusion criteria comprise terminally ill parents who are seeking palliative or hospice care and who are in contact with at least one child age 18 years or older. Dyads of parents and children related through adoption or fosterage will be included. Having received comprehensive oral and written information about the nature, the content and aim of the study, and about study participation, both patient and FM/s provide written informed consent in order to be eligible to participate as a dyad in this project. Individuals of both sexes and all ethnic backgrounds independent of their main diagnosis may participate in the study when fulfilling eligibility criteria.

Patients and FMs will be excluded from study if they are cognitively impaired (e.g., patients with dementia), or if they are not sufficiently proficient in German.

Termination criteria include significant emotional distress during the interview and insufficient cognitive abilities to answer interview questions and/or questionnaires (a Mini-Mental-State Examination [32, 33] score < 24).

Inclusion, exclusion, and termination criteria apply to patients of both dyads and the respective dyadic partner (i.e., adult child/parent). In the case of the patient’s death prior to study participation, no interviews will be conducted with the relative. Already collected interview data will be discarded respectively. If FMs have not been interviewed at the time of the patient’s death but data exist for the deceased, FMs will be invited to participate after their loved one’s death. If they withdraw their study participation, the deceased’s data will be discarded.

### Data analysis

Starting point for dyadic data analysis is what might be termed the concept of “nonindependence” as outlined by Kenny et al. [34]: “Two members of a dyad are not simply two independent individuals. Rather, they share something in common that we refer to as *nonindependence*.” The mixed-methods design enables developing a comprehensive picture of the dyads: Questionnaire data will be used to describe participants and to distinguish potential sub-types within both dyads. For instance, one may explore whether dyads with high versus low scores in loneliness describe different communication barriers. This demarcation of dyad types will help draw conclusions regarding risks and challenges in E-o-L care for specific groups.

Interviews will be transcribed verbatim by research assistants, coded by two independent researchers, and consented by a third researcher. All interviews will be analyzed qualitatively in MaxQDA [35] using methodological principles of Grounded Theory [36, 37]. This method is suitable to investigate social phenomena which are rather unknown so far. Grounded Theory allows a systematic understanding of peoples’ experiences and attitudes and is feasible even in vulnerable populations [38]. The bottom-up analysis technique allows to systematically code single text phrases (so-called “codes”) and to continuously summarize similar codes into more superior concepts. Finally, overall categories arise inductively. The current study will develop a code system for each unit of analysis which allows both intragroup comparisons within the dyads *terminally ill children and healthy parents* and *terminally ill parents and healthy children* and intergroup comparisons between the two dyads (see Fig. 1). From this structure, hypotheses can be built with regard to the addressed social phenomena. In a following step, a theoretical framework can be developed. This framework discloses main principles and connections between several aspects and assists in finding starting points for practical conclusions and ideas for interventions. Coding of interviews will take place in an iterative process in which interviews will be coded once conducted. The interview guide will be modified accordingly in the course of data collection if necessary.

**Fig. 1 Fig1:**
[figure not shown]
Development of code structure

The results of the “Grounded Theory” which are raised inductively from interview data will be augmented by results from standard questionnaires on loneliness, attachment, social support, and emotional closeness to enable a more detailed description of the study population. These well-established questionnaires will be applied to broaden the spectrum of information and to supplement the qualitative data, thus focusing on both depth and breadth of information [39], which is particularly beneficial for a small sample size. Quantitative data will be entered for statistical evaluation into the program IBM SPSS Statistics 24 (SPSS Inc., Chicago, IL, USA) for Windows and will then be analyzed according to the existing manuals. Prior to the main analysis, data cleaning and primary analysis will take place. Accuracy of data entries will be ensured through a series of steps [40], including evaluation of item range, checking for outliers, and calculation of univariate and bivariate statistics. Scale reliability will be assessed for all relevant variables. Descriptive statistics will be calculated to test assumptions of normality in the relevant outcome variables. Potential outliers will be examined. T-tests and chi-square tests will determine any group differences on demographic and outcome variables.

Finally, clinical conclusions on specific psychosocial care and support needs will be drawn. The members of the multiprofessional scientific advisory board will assist in data interpretation and development of recommendations for psychosocial support interventions in two face-to-face meetings. Recommendations regarding specific need-based psychosocial interventions will be drafted and consented (online) by board members. Volunteers (i.e. former caregivers and FMs whose relative/s received hospice and/or PC treatment) will serve as patient representatives and be included in a workshop. In addition, results will be presented in a patient and FM group for validation.

Figure 2 provides an overview of the study design. The figure illustrates the applied method of the development of research hypotheses and a theoretical framework on the specifics, similarities, and differences of both groups using Grounded Theory with its final aim of generating recommendations about specific psychosocial care needs.

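### The plan starts from nonindependence within dyads but names only t-tests and chi-square tests for the questionnaires, with no pairing, family clustering or rule for several family members

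*Protocol article*

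**What the plan says.** - **Premise.** The Data analysis section opens its treatment of dyads by citing the principle that "Two members of a dyad are not simply two independent individuals".
- **Tests.** In the same section, in the paragraph after Figure 1, the only inferential methods named for the questionnaires are these: "T-tests and chi-square tests will determine any group differences on demographic and outcome variables". The text does not say whether the t-tests are paired or independent, which groups are compared, or whether the unit is the person or the family.
- **Comparisons of interest.** Study aims states: "Both within-dyad as well as between-dyad interaction will be investigated". Hypotheses 1 and 2 set patients against their own relatives. Hypothesis 3 reads: "Differences with regard to the specifics of the interaction can be found between the two dyads".
- **Family size.** Under Study population and data collection, where a patient has two parents or several adult children, "all eligible FMs will be invited to participate in the face-to-face interview and to complete questionnaires".
- **Use of the scores.** The same section continues questionnaire collection after interview saturation, in part so that hypotheses arising from the interviews can be tested. Data analysis otherwise gives the questionnaires a descriptive, supplementary role.

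**The concern.** The premise and the named method do not meet. An independent-samples t-test and a Pearson chi-square both require independent observations. A patient and that patient's own relative are matched, and two parents or siblings from one family are clustered.

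With positive correlation the error runs in two directions. Comparing patients with their own relatives as if unrelated makes the standard error too large, so real differences are missed. Comparing dyad types with all persons entered as separate cases makes it too small, so chance differences look real. The clinical conclusions on support needs are drawn straight after these analyses. The Conclusion also offers the protocol as the yardstick for judging later deviations, so the method it names should follow from its premise.

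**Working it through.** **Inputs from the protocol.** 12 to 20 families per dyad type; one or more relatives per patient.

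**Assumed, because the protocol gives none of these.** Two-sided 5% level; normal scores with equal variance in both roles; exchangeable within-family correlation ρ of 0.1, 0.3 or 0.5.

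**The plan's own figure.** 2 × 12 = 24 and 2 × 20 = 40, which matches the stated 24 to 40 patients and 24 to 40 relatives, at about one relative per patient. There is no power, alpha or effect size to reproduce.

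**Within dyads (n pairs).** The true variance of the difference in means is 2σ²(1 − ρ)/n. The independent test uses 2σ²/n. Its standard error is too large by 1/√(1 − ρ) = 1.05, 1.20 and 1.41. The large-sample type I error is 2Φ(−1.96/√(1 − ρ)) = 3.9%, 1.9% and 0.6%.

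**Between dyad types, persons pooled (m per family).** The true variance of a type mean is σ²[1 + (m − 1)ρ]/(nm). The test uses σ²/(nm). The design effect D = 1 + (m − 1)ρ is 1.1, 1.3, 1.5 for m = 2 and 1.2, 1.6, 2.0 for m = 3. The large-sample type I error 2Φ(−1.96/√D) is 6.2%, 8.6%, 11.0% for m = 2 and 7.4%, 12.1%, 16.6% for m = 3.

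**Simulation.** 20,000 replicates, 12 families per type; results with 20 families were nearly the same.

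| Test | ρ = 0.1 | ρ = 0.3 | ρ = 0.5 |
|---|---|---|---|
| Patient vs own relative, independent t-test | 4.0% | 2.2% | 0.8% |
| Patient vs own relative, paired t-test | 5.1% | 5.0% | 4.9% |
| Between types, patients only | 5.0% | 4.9% | 5.0% |
| Between types, dyad means | 4.9% | 4.9% | 5.1% |
| Between types, patient-minus-relative differences | 5.0% | 5.0% | 5.1% |
| Between types, patient and one relative pooled | 6.1% | 8.7% | 11.5% |
| Between types, two relatives per family as separate cases | 6.1% | 8.4% | 11.6% |
| Between types, patient and two relatives pooled | 7.5% | 11.9% | 17.5% |

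**Power for a within-dyad difference of 0.8 SD (independent vs paired).**

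| Families | ρ = 0.1 | ρ = 0.3 | ρ = 0.5 |
|---|---|---|---|
| 12 | 46% vs 47% | 46% vs 57% | 46% vs 71% |
| 20 | 70% vs 72% | 73% vs 82% | 75% vs 92% |

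**Chi-square.** The variance of a difference between matched proportions contains −2 × covariance/n, which the Pearson test omits. Its error for patients against their own relatives therefore has the same direction as that of the independent t-test. Its size was not computed.

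**The case against.** The strongest reply is that the sentence is under-specified, not wrong. The word t-test includes the paired test, and the stated premise makes a dyad-respecting reading natural. Nothing says that persons will be pooled. The article condenses a fuller plan, and the choice between paired and independent is a detail often left there. Much of this stands, and it rules out several stronger readings that a reader might infer:

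- **That the p-values are wrong for all three hypotheses.** Hypotheses 1 to 3 concern communication, illness information, burden, support and caregiving role. The Methods section assigns these to the interview, and the code system supplies the within- and between-dyad comparisons. Hypothesis 3 also compares different families, so one value per family holds 5%.
- **That separate tests cannot tell illness role from generation.** Suppose role has effect R and generation effect G, additively. Patient minus relative is then R + G where the child is ill and R − G where the parent is ill. A t-test of these differences between dyad types estimates 2G, the same contrast as a role-by-type interaction.
- **That the inflation is necessarily large.** At ρ = 0.1 the error is 4.0% within dyads and 6.1% with patient and one relative pooled. The highest figures need two relatives for every patient and all three people pooled, while the planned totals imply about one relative each.

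What the reply does not remove is this. The article does name its tests. A paired t-test has no place for a second parent or sibling, and no rule selects or combines relatives. The named chi-square is not valid for matched people. Testing on questionnaire data is explicitly planned, so this goes beyond missing detail.

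**Conclusion.** The point holds for the questionnaire comparisons, including the later testing of interview-derived hypotheses. The plan announces nonindependence and then names tests into which neither pairing nor family is carried. If they are run on individuals at nominal 5%, the type I error falls to between 4% and 0.8% within dyads. It rises to between about 6% and 17.5% between dyad types, depending on the correlation and the number of people pooled per family.

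These sizes rest on an assumed ρ of 0.1 to 0.5, equal variances and normal scores; with negative correlation the directions reverse. Severity is moderate: the study is exploratory, sets no power target, and uses the questionnaires to supplement the interviews.

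**What to change.** Replace the t-test and chi-square sentence in Data analysis with the following.

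- **Scale scores.** One linear mixed model per score (MIXED in the SPSS version already named), with family as the cluster and role (patient or relative), dyad type and their interaction as fixed effects. Put the within-family covariance on the residuals, for example as compound symmetry, because a random intercept cannot represent negative correlation.
- **Simpler equivalent for scale scores.** Average the relatives of one family first. Within dyads, use a paired t-test of patient against that average. Between dyad types, use t-tests on family-level means (patient and relative average weighted equally) or on patient-minus-relative differences.
- **Categorical items.** McNemar's test for binary items with one relative per patient. Otherwise use a clustered logistic model with a small-sample correction, since robust standard errors can be too small with 24 to 40 families.
- **Definitions.** State for each comparison which groups are compared and whether the unit is the person or the family.

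Cost: analysis wording and a family identifier on each record. No new measurements are needed.
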